#### Skin Imaging

Skin imaging will be conducted using an OCT system (VivoSight; Michelson Diagnostics Ltd) that uses a laser source of near-infrared wavelength (1305 nm; class 1M [EN 60825-1]). The system includes a dynamic mode whereby the principles of speckle variance OCT are used to visualize the microvasculature in the superficial dermis. A total of 120 images with 50-μm spacing will be acquired as a 6 × 6 × 2 mm^3^ (width × length × depth) stack. This technique will allow noninvasive characterization of the skin’s epidermal and blood perfusion properties prior to and following the thermomechanical manipulations [45]. Using OCT is noninferior to punch biopsy for skin characterization [46]. The OCT probe will be placed gently on the skin, maintaining a static position during acquisition. Spacers at the probe interface will be used to optimize the focal point of the epidermis during scanning.

#### Perceptual Assessments

Participants’ local thermal and comfort sensations will be assessed via Likert scales to establish time-dependent changes in subjective perceptions of cooling [47]. The Likert scales for thermal sensation, thermal comfort, and thermal acceptance were created based on the recommendations of Schweiker et al [48], using a ruler to draw a 100-mm horizonal line with evenly spaced anchors. Thermal sensation is measured on a 7-point scale from 1 (cold) to 7 (hot), with 4 as neutral. Thermal comfort used a 5-point scale ranging from 1 (comfortable) to 5 (extremely uncomfortable), and thermal acceptance used a 4-point scale ranging from 1 (clearly acceptable) to 4 (clearly unacceptable). Perceptual sampling will occur before and after the shear protocol (Figure 2).

### Statistical Analyses

Data will be assessed for normality of distribution with the Kolmogorov-Smirnov test. Within- and between-subject mean differences (n=35 with 95% CIs) as a function of mechanical stimulus temperature (ie, 36 ºC, 24 ºC, and 16 ºC), time (ie, varying levels depending on the variables’ sampling rate), and participant group (ie, young, older, SCI) will be analyzed. These independent and interactive effects will be assessed by means of 3-way mixed model ANOVAs (or Friedman tests) for biomarker expression, skin structural properties, biophysical properties (ie, imaging parameters), subjective thermal perceptions, and kinetic CoF. Post hoc analyses will be performed between shear stimulus temperatures, time, and participant groups based on the presence of main effects and using the Tukey test. Group-related covariables associated with sex, skin tone, and clinical status (applicable to SCI participants only) will be considered in all analyses to interpret the proportion of variance unexplained by the main effects (ie, temperature, time, and group) and their interactions.

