The sample size justification for this protocol is based on the power calculations from Gordon et al [35], using changes in the peak hyperemic response, which is a robust, repeatable response. Specifically, we will recruit a minimum of 18 participants per group, with target recruitment of 35 individuals, to allow for sufficient statistical power and to account for up to 50% dropout. Participants will be screened for study participation using a set of inclusion and exclusion criteria. The young and healthy participants will be aged 18 to 35 years and the older and healthy participants will be aged 55 to 70 years. The participants presenting with SCI will have an injury level within T1 to S1. The younger and older healthy groups will undertake regular physical activity (1-3 times per week), be nonsmokers and nonvapers, and be free from comorbidities that would preclude them from taking part, such as hypertension or Raynaud's disease. Both male and female participants will be recruited for a subanalysis on the influence of sex; we will also recruit individuals with different skin tones, ranging from light to dark, as assessed by the Fitzpatrick scale [36]. Stratified skin sampling will be used to determine whether there is an influence of skin tone on pressure and shear tolerance at the skin of the heel.

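### The Friedman fallback cannot test the group, interaction and covariate effects assigned to it, so any outcome moved to it has no stated test of how aging and SCI modulate cooling

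*Protocol article*

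**What the plan says.** All of the analysis text is in the protocol article, Methods, Statistical Analyses. It opens with a distribution check: "Data will be assessed for normality of distribution with the Kolmogorov-Smirnov test". It then names three factors:

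- "mechanical stimulus temperature (ie, 36 ºC, 24 ºC, and 16 ºC"), within participant, three levels;
- "time (ie, varying levels depending on the variables’ sampling rate"), within participant;
- "participant group (ie, young, older, SCI) will be analyzed", between participants, three levels.

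The next sentence assigns the method: the separate and joint effects of these factors "will be assessed by means of 3-way mixed model ANOVAs (or Friedman tests"). It applies this to biomarker expression, skin structure, imaging parameters, thermal perceptions and the kinetic coefficient of friction. The section closes by bringing sex, skin tone and, for SCI participants, clinical status into every analysis.

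The Introduction gives two aims. The second asks how aging and SCI change the pathways through which cooling acts on tolerance to shear. No nonparametric method other than Friedman is named.

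**The concern.** The parenthesis presents Friedman as interchangeable with a three-way mixed ANOVA. The two do not answer the same questions. The mixed ANOVA has a group term and interaction terms. Friedman compares the levels of one repeated factor, and that is all it does.

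The second aim is a group-by-temperature question. If an outcome goes to the fallback, the plan as written gives no test of that aim for it, and no way to bring in the covariables that it wants considered throughout. The likely candidates matter to the study: seven inflammatory biomarkers, whose distributions are often skewed, and three ratings with 7, 5 and 4 labelled points. For one of these, for example, "thermal acceptance used a 4-point scale ranging from 1 (clearly acceptable) to 4 (clearly unacceptable").

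**Working it through.** **Inputs from the document.** Three groups, three temperatures, a minimum of 18 and a target of 35 per group (Participants). The target is the minimum enlarged for dropout: 18 / (1 − 0.5) = 36, close to the stated 35. Nothing below changes that number.

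**Step 1: which effects each method covers.** Temperature (T), time (M) and group (G) give seven effects.

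| Effect | Three-way mixed ANOVA | Friedman |
|---|---|---|
| T | yes | yes, after collapsing or fixing time and ignoring group |
| M | yes | yes, after collapsing or fixing temperature and ignoring group |
| G | yes | no |
| T × M | yes | no |
| T × G | yes | no |
| M × G | yes | no |
| T × M × G | yes | no |
| Covariates | yes, if added | no |

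Two of the seven effects can be reached, one at a time. None of the four that involve group can be.

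**Step 2: why group drops out.** With N participants and k conditions, let R_j be the sum over participants of the within-person ranks of condition j. Then

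χ²_F = [12 / (N k (k + 1))] Σ R_j² − 3 N (k + 1).

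Adding a constant to all values of one participant leaves that person's ranks unchanged, so every R_j is unchanged. Numerical check with 18 per group (N = 54, k = 3): the statistic was 2.926. After adding 0, 5 and 10 units to the three groups it was still 2.926.

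**Step 3: size, by simulation.** Assumptions, none of them from the document: normal data, total SD 1 before effects are added, within-person correlation 0.5, one value per temperature, α = 0.05, 2000 runs. The interaction scenario uses slopes of −0.5, 0 and +0.5 SD per temperature step in the three groups. The group scenario uses a shift of 0.8 SD per group step.

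| n per group | Scenario | Friedman | T × G F test | Group F test |
|---|---|---|---|---|
| 18 | no effect | 5.45% | 4.95% | 5.05% |
| 18 | interaction only | 2.9% | 99.95% | 4.4% |
| 18 | group shift only | 4.85% | 4.5% | 99.85% |
| 35 | no effect | 5.3% | 5.45% | 4.6% |
| 35 | interaction only | 2.85% | 100% | 5.15% |
| 35 | group shift only | 4.8% | 5.35% | 100% |

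All tests hold their level when there is no effect. Friedman stays at or below about 5% when the only effect is the one the second aim is about, and a larger sample does not help.

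**The case against.** **The simulated interaction is a constructed case.** Opposite slopes cancel when groups are pooled, so a low Friedman rate is guaranteed. With effects in the same direction (0.8, 0.4 and 0.2 SD, 35 per group, correlation 0.5), pooled Friedman rejects in about 97% of runs. This stands: the temperature effect of the first aim remains testable, and the table illustrates an algebraic fact rather than forecasting harm. But that 97% reflects temperature, and the test cannot say whether the three groups differ.

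**Workarounds exist.** One could run Friedman within each group, or apply rank tests to within-person differences. Separate tests by group do not test a difference between groups, and the plan names no test on differences.

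**The unseen analysis plan may name something better.** It may. The point is not a missing detail, though: the article states a method for stated effects, and the method does not fit them.

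**The trigger is not written.** That the Kolmogorov-Smirnov result decides the switch is inferred from sentence order. This stands, but Friedman is unsuitable for these effects whatever triggers it.

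**The ratings may not be ordinal.** Perceptual Assessments also describes a 100-mm line with evenly spaced anchors, so they may be read as continuous. This stands, and the fix is conditional on it.

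Two stronger readings are tempting and should not be drawn.

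- *That the plan discards participants with missing sessions.* The Participants section sets the target "to allow for sufficient statistical power and to account for up to 50% dropout", and Friedman needs complete blocks. But no listwise rule is written, and a mixed model ANOVA may be a likelihood-based model that keeps partial data. The timing of dropout is not given, and handling of missing sessions may sit in the analysis plan. Any figure for lost precision would rest on an assumed dropout pattern.
- *That the Kolmogorov-Smirnov test almost never rejects at these sample sizes.* The rate depends on the variant and the n, and the article fixes neither. For assumed lognormal data (log-SD 0.8), the plain test with estimated mean and SD rejects in about 30% to 34% of samples at n = 35 and 96% at n = 105. The Lilliefors version rejects in about 58% at n = 18 and 86% to 89% at n = 35.

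**Conclusion.** The concern holds for the Friedman fallback. It is offered for group, interaction and covariate effects that it cannot test. Every outcome analysed by it would have no stated test of the second aim. That conclusion is algebraic and needs no assumption about effect size. The simulated contrast (about 3% against over 99%) is an illustration that rests on the assumed slopes, correlation and normal data.

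How many outcomes would take this route cannot be derived from the article, because the switching rule, the test variant and the scoring of the ratings are not fixed there. Outcomes that stay with the mixed ANOVA are unaffected. The documents do not support extending the point to complete-case analysis or to a normality test that never rejects.

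**What to change.** In Statistical Analyses:

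- Delete the Friedman option as a substitute for the three-way model.
- For biomarkers, name the same mixed model (temperature, time, group, their interactions and the covariables) on log-transformed values.
- For the ratings, name an ordinal mixed model with the same terms if they are scored as categories. If they are read in millimetres from the line, keep the mixed model and say so.
- If a nonparametric check is wanted, use a factorial rank method for longitudinal data to check group and interactions.
- Choose the method by outcome type and residual checks, not by a Kolmogorov-Smirnov test on the data.

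The article reports that data collection and analysis are under way, so the change should be made and dated now. It costs wording and standard software and leaves the sample size as it is. The downside is in reporting: log-scale effects become ratios, and ordinal effects become odds ratios.

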**Methods:**

The protocol will be tested on individuals of different age, sex, skin tone, and comorbidities, using a repeated measures design. Three cohorts will be recruited: (1) young and healthy (n=35), (2) older and healthy (n=35), and (3) with spinal cord injury (n=35). Participants will complete 3 testing sessions using a custom-built shearing rig with integrated thermal plate, during which the posterior aspect of the heel will be exposed to a standardized mechanical stimulus to elicit repeated pressure and shear loading. The experimental condition of each session will be determined by the temperature of the thermal plate, which will be set to either 36 °C (no cooling), 24 °C (mild cooling), or 16 °C (strong cooling). Continuous measurements will include kinetic coefficient of friction (CoF) and skin blood flow (via laser Doppler flowmetry; 40 Hz). Pro- and anti-inflammatory biomarkers in skin sebum (via Sebutape), structural skin properties (via optical coherence tomography), skin conductance (in microsiemens) and ratings of thermal sensation, comfort, and acceptance (via Likert scales) will also be assessed before and after the shear stress protocol.

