## Methods

### Overview

Participants will attend 3 experimental sessions separated by a minimum of 24 hours in the Clinical Academic Facility located at Southampton General Hospital (Southampton, United Kingdom). During the sessions, participants will place the center of their posterior heel on a custom-built friction rig with an integrated thermal plate to undergo a standardized protocol eliciting repeated pressure and shear force. The study will use a randomized crossover design involving 3 plate temperatures: 36 ºC (no cooling), 24 ºC (mild cooling), or 16 ºC (strong cooling). Microclimate conditions at the interface between a loaded skin site at risk of pressure ulcer (eg, the sacrum) and a support surface (eg, a mattress) are commonly associated with skin temperatures of approximately 38 ºC. Following pilot testing, some participants (n=2) found a 38 ºC plate temperature to be borderline uncomfortable, so we decided to reduce the plate temperature to 36 ºC to improve thermal tolerability in the no cooling condition. The rationale for using 2 levels of cooling was 2-fold: first, prior research investigating localized cooling on tissue viability in animal models [17,18] used cooling interventions at 25 ºC, demonstrating the benefit of reduced skin temperature in preserving tissue viability. Second, one of the main aims of the study is to examine how different levels of cooling may influence the biophysical properties of the skin and perceptual thermal tolerances of both mild (24 ºC) and strong (16 ºC) cooling.

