**Figure 1 figure1:**
[figure not shown]
Experimental set up. The foot and ankle are supported by an orthotic brace and ankle support to standardize positioning while minimizing movement during the shearing protocol.

A series of measurements that run continuously or during discrete time points will be taken (Figure 2). First, baseline assessments, including structural and functional imaging of the posterior heel skin, will be captured using optical coherence tomography (OCT). This will be followed by sampling of skin sebum at the heel for subsequent biomarker analysis, using an established methodology involving a 2-minute application time and tweezer extraction to avoid cross contamination [38]. To provide an index of baseline local skin hydration, a capacitance meter will then be placed on the heel to measure skin conductance (in microsiemens). After the baseline measurements are completed, participants will place the heel on the thermal plate of the shearing rig [13]. The temperature of the aluminum thermal plate (22 × 16.7 cm) is controlled by a set of Peltier elements, and when applied to the skin, allows for the manipulation of local skin temperature (range 0 °C to >50 °C; variable temperature rates under PID control [Daisylab; MC Computing]). An optical fiber is integrated in the center of the plate through a 1-mm hole flush to its surface, allowing for the monitoring of skin blood flow via laser Doppler flowmetry (LDF) when the heel is static. An integrated force plate and low resistance trackway allow the recording of both normal and tangential forces (in newtons), respectively. The friction rig is interfaced with an analogue-to-digital data acquisition unit (MC Computing), sampling plate surface temperature (°C), normal forces, and tangential forces at 33 Hz. The kinetic coefficient of friction (CoF) according to Amonton’s law [39] can be estimated as the ratio of tangential to normal force and defined as the resistance generated from 2 surfaces rubbing against each other [40].

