The protocol starts by participants placing the heel in the center of the thermal plate over the hole, where the LDF optical probe is located flush to the surface. Positioning of the bed and lower limb will be modified to provide a standardized 15-N axial load on the plate. Skin blood flow will be measured intermittently (accounting for displacement of the heel following the static loading phases) throughout the protocol via LDF (moorVMS-LDF laser Doppler monitor; Moor Instruments). The heel will remain in place for a 60-second thermal preconditioning period to allow for temperature adaptation at the skin interface (at 36 °C, 24 °C, or 16 °C). The repeated shearing sequence will then commence (Figure 2), initially with a 10-second pause, before the servomotor travels in one direction pulling the rig and displacing it by 10 cm, pausing for 1 second, then traveling in the opposite direction, pushing the rig back to the original starting point. This sequence completes one repetition, which is repeated 10 times. After completing the 10 shearing repetitions, participants’ thermal perceptions will be recorded, followed by posttest OCT, skin sebum, and skin conductance measurements.

The sections below provide a description of the measurements to be used during the protocol.

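### For outcomes read before plate contact in each session, the baseline enters as a level of time and not as a covariate, so the temperature x time contrast is valid but less precise than it could be

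*Protocol article*

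**What the plan says.** The Overview section sets the design: "The study will use a randomized crossover design involving 3 plate temperatures", one temperature per session. Experimental Procedures gives the order of measurement within a session. "First, baseline assessments, including structural and functional imaging of the posterior heel skin, will be captured"; sebum sampling and skin conductance follow. Only then does the heel meet the plate: "After the baseline measurements are completed, participants will place the heel on the thermal plate of the shearing rig". After the ten shear repetitions, thermal perceptions are recorded, "followed by posttest OCT, skin sebum, and skin conductance measurements". The abstract agrees that these measures "will also be assessed before and after the shear stress protocol".

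Statistical Analyses names three factors: plate temperature, participant group and "time (ie, varying levels depending on the" sampling rate of each variable. Their separate and joint effects are to be "assessed by means of 3-way mixed model ANOVAs (or Friedman tests) for biomarker expression, skin structural properties", imaging parameters, thermal perceptions and kinetic coefficient of friction. On covariates it says: "Group-related covariables associated with sex, skin tone, and clinical status (applicable to SCI participants only) will be considered in all analyses".

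**The concern.** For an outcome sampled only before and after shear, time has two levels and the pre-plate reading is one of them. It therefore sits on the outcome side of the model. The named covariables are all characteristics of the person, so their main effects cannot absorb session-to-session noise in a within-person comparison of temperatures.

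With two time levels, the temperature x time contrast equals the difference between sessions in post minus pre. This fixes the slope on baseline at 1, whatever the data show. Noise in one session's baseline reading, such as tape yield, probe position or skin hydration, is subtracted at full weight. Temperature order is randomised and the reading precedes plate contact, so that session's temperature cannot have affected it. It would be a legitimate covariate.

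At stake is the precision of the temperature comparisons that serve the first aim, and of their differences between groups, which serve the second.

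**Working it through.** **The plan's own figure.** Participants gives a minimum of 18 per group, a target of 35 and up to 50% dropout. 18/(1-0.5) = 36, and 35 x 0.5 = 17.5, so the target is reproduced to within rounding. The 18 cannot be rebuilt, because the article refers to the companion protocol for its power calculation and gives no effect size, standard deviation or power.

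**Assumptions.** Pre and post readings have equal within-session variance s2. The crossover removes stable differences between people, so r is the within-person, session-level pre-post correlation. The article gives no r, so a range is shown. The 80% reference power for the change-score contrast is also an assumption.

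**Variance per session**

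- Change score: Var(post - pre) = 2 x s2 x (1-r).
- Baseline-adjusted: s2 x (1-r^2).
- Ratio, adjusted to change: (1-r^2)/[2(1-r)] = (1+r)/2, which is below 1 for every r below 1.

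**Power with adjustment** = Phi(2.802/sqrt(ratio) - 1.96), where 2.802 = 1.960 + 0.842 is the standardised effect that gives 80% for the change score. At r=0.5: 2.802/sqrt(0.75) = 3.236; 3.236 - 1.96 = 1.276; Phi = 0.90.

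| r | Change, 2(1-r) | Adjusted, 1-r^2 | Ratio | Power, change (assumed) | Power, adjusted |
|---|---|---|---|---|---|
| 0.2 | 1.60 | 0.96 | 0.60 | 80% | 95% |
| 0.5 | 1.00 | 0.75 | 0.75 | 80% | 90% |
| 0.7 | 0.60 | 0.51 | 0.85 | 80% | 86% |
| 0.8 | 0.40 | 0.36 | 0.90 | 80% | 84% |
| 0.9 | 0.20 | 0.19 | 0.95 | 80% | 82% |

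In terms of people, at r=0.5 the change-score analysis of 18 has the precision of 18 x 0.75 = 13.5 people with adjustment; for 35 it is 35 x 0.75 = about 26.

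**Simulation.** Two independent simulations used 18 people, 3 sessions, a person effect and the 16 versus 36 °C contrast, with 4,000 replicates for power. Change score against adjusted gave 79% against 93-94% at r=0.2, 80% against 88-90% at r=0.5, 79-81% against 84-85% at r=0.7, and 80% against 83% at r=0.8. Type I error was about 4-6% for both methods.

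**Other contrasts.** A comparison of post-shear values alone has variance s2. That is 1.00 against 0.96 adjusted at r=0.2, 1.00 against 0.75 at r=0.5 and 1.00 against 0.51 at r=0.7. The temperature main effect averages in a pre level that the session's cooling cannot have changed. The average has variance s2 x (1+r)/2 and carries half the effect, so on the scale of the post-shear effect its variance is 4 x s2 x (1+r)/2 = 2 x s2 x (1+r), or 3.0 at r=0.5.

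**The case against.** The planned model is valid. Order is randomised, the interaction contrast is unbiased and its type I error is correct. This stands: the point is about precision only, and a reader who inferred bias would be wrong.

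The covariate sentence speaks of group-related covariables, so it does not rule out a session-level covariate, and an article condenses a fuller plan. That is fair as far as it goes. However, the article states the model, its factors and its covariables, and as stated the baseline is a time level.

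The Tukey comparisons are triggered by main effects and are not defined as change scores. This also stands, and it limits the exact equivalence to the temperature x time contrast. If the comparison were of post-shear values alone, the gain from adjustment at r=0.2 would be 4% of variance and not 40%. Neither alternative rescues precision in general, since post-only is worse than the change score above r=0.5 and the main effect has larger variance than the adjusted contrast at every r.

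A reader might infer that every cooling interval is too wide. The article does not support that. Kinetic friction has no pre-plate value. The laser Doppler baseline is taken on the plate at the allocated temperature. The first perceptual ratings are described after heel placement. Skin conductance is read before and after, but is not named in the list of ANOVA outcomes. The sample size rests on peak hyperemic response, so the stated power basis is untouched.

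Finally, replacing the time analysis with a post-shear model alone would give up inference on whether shear changed the skin and whether that differs by group. This is a sound objection to replacement, and the fix below adds a model instead.

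**Conclusion.** The point holds for sebum biomarkers and OCT parameters, and for skin conductance if it is analysed in the same way. For these, the stated model turns the temperature x time contrast into a change-score contrast, which has more variance than a baseline-adjusted contrast whenever r is below 1. Adjustment removes 40% of the variance at r=0.2, 25% at r=0.5, 15% at r=0.7 and 10% at r=0.8.

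These sizes rest on equal pre and post variance, a linear relation between the two readings, and the assumed 80% reference power. A material loss is possible but not demonstrated, because the article does not show where r lies. Since the crossover already removes stable differences between people, r may be modest, which is where the gain is largest. It would be going too far to conclude that the study is underpowered or that its planned analysis is invalid. This is a nearly free improvement.

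**What to change.** Keep the temperature x time x group model for inference on the response to shear and on how that response differs by group.

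For the randomised temperature contrasts and temperature x group, add a mixed model for each outcome with a pre-plate reading:

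- Outcome: the post-shear value, transformed where skewed.
- Fixed effects: temperature, group, temperature x group and period.
- Random effect: participant.
- Covariates: the session's pre-plate value, split into the participant's mean over sessions and the session's deviation from that mean. The deviation supplies the precision, and the split keeps baseline differences between the non-randomised groups out of the temperature contrasts.

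Do not use the laser Doppler preconditioning value as a baseline covariate, because it is measured at the allocated temperature. Fix the wording before results are examined; the article reports data collection and analysis as ongoing.

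The cost is one or two degrees of freedom per outcome and a little more analysis work. No new data or procedures are needed.
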